### Handling of missing values in rank ANCOVA

Patients with missing values due to death will be assigned the worst ranks according to the time from randomization until death where the shortest time until death corresponds to the worst rank.

A missing value at Visit X in Patient A who is alive at that time will be imputed as follows. For patients without any missing values from baseline up to Visit X the sum of squared differences (SSD) between each patient and Patient A is calculated across all values from baseline up to one visit before Visit X. The three patients with the smallest SSD will be taken into account for imputing the missing value for Patient A at Visit X by taking the average value of the three patients at that visit.

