### Study endpoints

Efficacy will be assessed by the absolute change in percent predicted FVC from baseline to week 48 using a rank analysis of covariance (ANCOVA) model.

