#### A number of key secondary endpoints were defined:

Time to disease worsening, defined as time to clinical deterioration, lung fibrosis-related death, lung transplant or respiratory hospitalization, whichever comes first

For the purpose of this study, clinical deterioration is defined as follows:Clinically worsening of dyspnea within 4 weeks andNew or worsening radiographic abnormalities on chest x-ray or HRCT andObjective worsening of PFT or gas exchange defined by at least one of the following criteria- Initiation of LTOT or increase of oxygen supplementation of existing LTOT by ≥1 l/min to maintain resting oxygen saturation (SaO_2_) ≥ 90%.- Drop in FVC by >10% as compared to last measurement- Drop in DLCO by >15% as compared to last measurement- Drop in 6MWD by 20% as compared to last measurementProgression-free survival, defined as time to the first occurrence of either of the following (as compared to the patient’s baseline):- ≥ 10% absolute decline in percent predicted FVC- ≥ 15% absolute decline in percent predicted Hb-corrected DLCO- Death of the patientCategorical assessment of relative change from baseline to week 48 in percent predicted FVC.Change from baseline to week 48 in SGRQ and EQ-5D.Change from baseline to week 48 in the percent predicted Hb-corrected DLCO/TLCO.Change from baseline to week 48 in the worst oxygen saturation by pulse oximetry (SpO2) measurement observed during the 6MWT.Change from baseline to week 48 in distance walked in the 6MWT.Assessment of safety including overall mortality.

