Additionally, the following inclusion criteria were defined:Women of childbearing capacity are required to have a negative serum pregnancy test before treatment and must agree to maintain highly effective methods of contraception by practicing abstinence or by using at least two methods of birth control from the date of consent through the end of the study. If abstinence is not practiced, then one of the two methods of birth control should be an oral contraceptive (e.g., oral contraception and a spermicide)Percent predicted FVC ≥ 40%, but <90% at the Screening Visit (before randomization)Percent predicted, hemoglobin (Hb)-corrected carbon monoxide diffusing capacity/carbon monoxide transfer capacity (DLCO) ≥ 25%, but <75% at the Screening VisitDistance walked ≥150 m, with O_2_ saturation > 83% on ≤6 L/min of O_2_
Able to understand and sign a written informed consent formAble to understand the importance of adherence to study treatment and the study protocol, including the concomitant medication restrictions throughout the study periodPatients being considered or on the waiting list for lung transplantation are eligible for participation only if their estimated waiting time is longer than the study period. At the time these patients are placed on the list the date and reason for this placement and the Lung Allocation Score (LAS) should be collected

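### Lung transplant is a failure in time to disease worsening, a non-event in progression-free survival, and ordinary missing or usable data in the primary analysis

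*Protocol article*

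**What the plan says.** All references are to the Protocol article.

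- **Primary endpoint** (*Study endpoints*): "absolute change in percent predicted FVC from baseline to week 48 using a rank analysis of covariance (ANCOVA) model".
- **Missing values** (*Handling of missing values in rank ANCOVA*): the rule has two branches. For death, "Patients with missing values due to death will be assigned the worst ranks according to the time from randomization until death", with no restriction on cause. For the living, "A missing value at Visit X in Patient A who is alive at that time will be imputed as follows": the three patients with complete values up to that visit and the smallest squared distance on earlier values are found, and the gap is filled "by taking the average value of the three patients at that visit". Transplant is not mentioned in either branch.
- **Time to disease worsening** (key secondary endpoints): "defined as time to clinical deterioration, lung fibrosis-related death, lung transplant or respiratory hospitalization, whichever comes first".
- **Progression-free survival** (same list): "defined as time to the first occurrence of either of the following", followed by three items: an absolute FVC decline of at least 10% predicted, an absolute DLCO decline of at least 15% predicted, or death. Transplant is not among them.
- **Eligibility**: under *Study population*, patients considered or listed for transplant "are eligible for participation only if their estimated waiting time is longer than the study period". *Disease-Related Exclusions* also bars patients whom the investigator expects to need, and be eligible for, a transplant within 52 weeks of randomization.

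**The concern.** The same event has three statuses. Under the progression-free survival definition, a patient transplanted without an earlier qualifying FVC or DLCO decline has no event on the transplant date. That patient remains event-free until death or until a later measurement falls far enough below the pre-transplant baseline, and a donor lung makes such a fall less likely. The same patient is a failure in the neighbouring endpoint on that date.

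In the primary analysis there are two routes. If the FVC is missing, the living-patient branch applies and the value is borrowed from patients with similar earlier values. If an FVC was measured after transplant, it is not missing, so the rule is silent and the donor-lung value could be ranked as the patient's own change from baseline.

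What is at stake is a consistent meaning of treatment failure across the primary and key secondary endpoints. If transplants occur, a result that depends on which definition was followed is also at stake.

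**Working it through.** **1. The plan's own figures.** Inputs from *Sample size* and *Interim analysis*: effect size 0.3, two-sided 5%, power 80%, factor π/3, one O'Brien-Fleming interim at 224 patients, 187 per arm.

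- Fixed design: 2 × (1.960 + 0.842)² / 0.3² gives 175 per arm; × π/3 = 183.3.
- Two looks at information fraction 224/374 = 0.60: 176.7 × π/3 = 185.1 per arm, against 187 stated.
- Interim level 0.0101, interim power about 35% and overall power at 187 per arm 80.4%, in line with the stated 0.0101, about 35% and 80%.

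No stated number is wrong on this point.

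**2. One event, three endpoints.**

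| Endpoint | Transplant | Death |
|---|---|---|
| Time to disease worsening | Event | Event if lung fibrosis-related |
| Progression-free survival | Not listed | Event, any cause |
| Primary rank ANCOVA | Missing FVC: mean of three similar patients. Measured FVC: no rule | Worst ranks if FVC is missing, any cause |

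**3. Possible size in the primary analysis.** The document gives no transplant count, so 0 to 8 per arm is an assumption (4/187 = 2.1%, 8/187 = 4.3%). I simulated 4,000 trials per scenario with normal outcomes, 187 per arm, a shift of 0.3 SD and a single rank test at two-sided 5%. *Imputed* gives a transplanted patient the mean of three same-arm patients. *Worst-ranked* puts transplants at the bottom.

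| Transplants, placebo/pirfenidone | Power, imputed | Power, worst-ranked | Difference (points) |
|---|---|---|---|
| 0/0 | 80.6% | 80.8% | +0.2 (noise) |
| 4/0 | 81.1% | 87.4% | +6.3 |
| 4/2 | 80.2% | 84.3% | +4.1 |
| 8/4 | 80.7% | 86.8% | +6.1 |
| 4/4 | 80.9% | 77.4% | −3.5 |
| 0/4 | 80.5% | 68.8% | −11.7 |

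Simulation error on each power is √(0.8 × 0.2 / 4000), about 0.6 points. With no treatment effect in the other patients, imputation rejected in 4.8% to 5.8% of runs (error about 0.3 points), so it does not visibly inflate type I error.

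**4. Limits.** The simulation draws the three patients at random within the arm. The protocol matches on earlier values and does not restrict the match to the same arm. The simulation has no covariate and no interim look, and it does not model FVC measured after transplant. It shows direction and order of size only.

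**The case against.** The strongest reply is that this hardly matters. Anyone expected to need a transplant within 52 weeks is excluded, which covers the 48-week endpoint, and listed patients need an expected wait beyond the study. Imputation keeps power and type I error close to plan, whereas worst-ranking can cost power. Handling of values after transplant is the kind of detail an article leaves to the analysis plan, which is not shown.

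Much of this stands. Transplants should be few, although both eligibility rules are forecasts made at entry and do not rule them out. The silence on FVC after transplant may be resolved elsewhere. But the missing-value rule and the progression-free survival event list are stated, and following them as written produces the inconsistency.

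A reader might infer more than the document supports:

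- *That deaths from other causes are censored.* No censoring rule is printed. *Secondary endpoints* names Kaplan-Meier only as an example and defers further analyses to the analysis plan. Deaths of any cause count in progression-free survival, and deaths with missing FVC take worst ranks whatever the cause. A fibrosis-specific component in time to disease worsening is a defensible choice beside an all-cause one.
- *That transplanted patients are scored as stable.* The imputed value follows three patients with a similar earlier course and can show decline.
- *That the primary effect is biased toward zero by a known amount.* This needs a transplant rate in each arm, and none is given.

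**Conclusion.** The point holds as an inconsistency in stated definitions. Lung transplant is failure in one key secondary endpoint, is absent from the event list of another, and has no place in the primary missing-value rule beyond that of any living patient with a gap. It is not shown to bias the primary result materially. Under assumed counts of up to 8 per arm, the choice between imputing and worst-ranking moves power by between −11.7 and +6.3 points. The sign depends on which arm has more transplants, and with no transplants the choice has no effect. The argument for change is therefore that a treatment failure should be classified consistently, not that power will improve.

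**What to change.** 1. **Progression-free survival:** add lung transplant as an event, dated at transplant.
2. **All lung-function endpoints:** state that FVC and DLCO measured after transplant are not used.
3. **Primary rank ANCOVA:** rank transplant together with death by time from randomization to the event, at least as a prespecified sensitivity analysis beside the current imputation rule.

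**Cost:** wording only, provided it is fixed before unblinding. Transplant is already a component of time to disease worsening, so its date has to be collected anyway. Items 1 and 2 have almost no downside. Item 3 lowers power if transplants are equal between arms (81% to 77% at 4 versus 4 in the illustration) or more frequent on pirfenidone (81% to 69% at 0 on placebo versus 4 on pirfenidone). That is why a sensitivity analysis is enough if the sponsor prefers to leave the primary rule as it is.

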## Background

In the years 2011–2015, the anti-fibrotic drug pirfenidone (inhibitor of TGF-β, TNF α and of PDGF) and the triple kinase inhibitor nintedanib (inhibitor of PDGF, VEGF, and FGF) have both been approved for treatment of Idiopathic Pulmonary Fibrosis (IPF) in the European Union as well as in the United States. IPF is the most frequent and aggressive diffuse parenchymal lung disease (DPLD) in the western world. In well-designed clinical phase III trials, both drugs have been demonstrated to reduce the annual loss of FVC by approximately 50% and to yield a significant reduction of all-cause mortality after one year for pirfenidone [1–4]. Of note, there are several DPLDs which share pathomechanistic principles, e.g. disturbed epithelial-mesenchymal crosstalk, radiographic/histological characteristics like reticulation, traction bronchiectasis and honeycombing in variable combinations, as well as the progressive worsening and the fatal outcome with IPF and, therefore, represent important differential diagnoses and areas of great unmet medical need. Among these are lung fibrosis in association to collagen/vascular diseases (CVD-LF), fibrotic non-specific interstitial pneumonia (fNSIP), chronic hypersensitivity pneumonitis (cHP), and asbestos-induced lung fibrosis (ALF) [5–12]. In these entities, immunosuppressive therapy represents the standard clinical treatment option, albeit frequently ineffective and potentially harmful. In case of ALF, no pharmacological treatment is available at all. Therefore, a novel treatment option is highly needed for these most severely impaired patients.

We hypothesized that, based on the pathophysiological and clinical similarities between IPF and the mentioned four types of non-IPF lung fibrosis, pirfenidone should be a viable treatment option especially in patients in whom conventional anti-inflammatory therapy failed. In particular, we aim to assess whether treatment with pirfenidone results in attenuation of the decline in lung function and exercise capacity in these patients, similarly to what has been observed in IPF. We will therefore conduct an exploratory efficacy and safety study of oral pirfenidone for progressive, non-IPF lung fibrosis (RELIEF in LUNG FIBROSIS) in CVD-LF, fNSIP, cHP, and ALF.

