### Secondary endpoints

Secondary outcomes will be analyzed by using appropriate statistical methods, e.g. Kaplan-Meier estimates and rank ANCOVA. Additional analyses will be described in detail in a statistical analysis plan (SAP) before data base closure.

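### In the primary FVC analysis, living patients too ill from lung disease to be tested get the mean of three tested, matched patients, which scores them too favourably

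*Protocol article*

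**What the plan says.** The section on missing values in rank ANCOVA defines two classes. Patients who die take the worst ranks, with the earliest death ranked lowest. For all others: "A missing value at Visit X in Patient A who is alive at that time will be imputed as follows".

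Donors are limited to patients with a complete record: "For patients without any missing values from baseline up to Visit X the sum of squared differences (SSD) between each patient and Patient A is" the matching quantity. The distance "is calculated across all values from baseline up to one visit before Visit X", the three nearest donors are kept, and the gap is filled "by taking the average value of the three patients at that visit". Neither the reason for the gap nor any non-fatal event enters the rule.

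Rank ANCOVA is the method for the primary endpoint, absolute change in percent predicted FVC to week 48 (Study endpoints; Primary endpoint). The main analysis set is every randomised patient (Analysis population), so gaps have to be filled. For the other endpoints the text is looser: "Secondary outcomes will be analyzed by using appropriate statistical methods, e.g. Kaplan-Meier estimates and rank ANCOVA".

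**The concern.** At entry, patients who cannot perform lung function tests are excluded and a walk of at least 150 m is required. Inability at a later visit is therefore a new loss of function. Where lung disease is the cause, it is an outcome and not a random gap.

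The rule already accepts this logic for death. A patient who dies shortly before week 48 is ranked at the bottom, while one who is alive but cannot blow receives a value from patients who could. Every donor is testable by construction, so nobody in the untestable patient's condition can be a donor. The trial selects patients with documented progression, so such survivors are foreseeable.

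At stake is the primary comparison, which would partly lose the worst non-fatal outcomes. Exercise capacity could also be affected if the rule extends to the walk test, since the Background names among the aims "attenuation of the decline in lung function and exercise capacity in these patients".

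**Working it through.** **The plan's own figure.** The rule carries no number. The sample size it serves reproduces: 175.4 per arm for a t test (effect 0.3, two-sided 5%, 80% power) × 1.0133 for the O'Brien-Fleming interim at 224/374 = 177.7, rounded up to 178; 178 × π/3 = 186.4, so 187. Nothing in it depends on the imputation rule.

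**Step 1: what each patient receives.**

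| State at week 48 | Score under the rule |
|---|---|
| Died | Worst rank, by time of death |
| Alive, value missing for an unrelated reason | Mean of three matched, tested patients |
| Alive, too ill from lung disease to test | Mean of three matched, tested patients |

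**Step 2: how far off the third row is.** From the protocol: 374 patients and the three-donor rule. Assumed, because the article gives no figures:
- FVC at weeks 0, 12, 24, 36 and 48; baseline mean 65, SD 13; mean 48-week change -5 points, SD of change about 7 to 9.
- Three mixes of variation (SDs of slope / noise / visit-to-visit shock): 6/2/1, 4/2.5/2 and 2/2.5/4.
- The worst 8% by true change are untestable. Successive gaps are filled in order, each filled value then being used for matching.
- No deaths and no treatment effect.

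The worst 8% occupy percentiles 0 to 8, so their true mean percentile is about 4. Ranges run over the three mixes, 100 simulated trials each.

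| Missing from | True mean change | Imputed mean change | Percentile given |
|---|---|---|---|
| Week 48 only | -17.4 to -21.7 | -10.5 to -12.5 | 14-19 |
| Second post-baseline visit | -17.4 to -21.7 | -6.7 to -7.6 | 33-38 |
| First post-baseline visit | -17.5 to -21.7 | -3.9 to -4.5 | 49-50 |

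Tested patients average -3.5 to -4.0. The score is too favourable in every row, and more so the earlier testing stops, because fewer of the patient's own values remain to match on.

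**Step 3: what this does to the comparison.** Let θ be the chance that a random pirfenidone patient does better than a random placebo patient. With equal arms, θ = 0.5 + the difference in mean percentile (as a fraction). Let fD and fP be the untestable fractions on drug and placebo, f their average and p the mean percentile given to untestable patients. If tested patients are alike in both arms, their mean percentile is (0.5 - f·p)/(1 - f), so

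θ = 0.5 + (fD - fP)(p - 0.5)/(1 - f).

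Take fD = 0.10 and fP = 0.05 for illustration, so f = 0.075:
- Ranked at the bottom, p = 0.04: 0.5 + 0.05 × (-0.46)/0.925 = 0.475.
- Week 48 only, p = 0.14 to 0.19: 0.481 to 0.483.
- From the second visit, p = 0.33 to 0.38: 0.491 to 0.494.
- From the first visit, p = 0.49 to 0.50: about 0.500.

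A simulation with this split (150 trials per setting) agrees: 0.478-0.485, 0.488-0.492 and 0.496-0.501, against 0.470-0.477 on the true values. With the arms exchanged the figures mirror: a true 0.525 reads 0.517-0.519, 0.506-0.509 and about 0.500. With equal fractions the shift is zero.

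For scale, the planned effect of 0.3 SD on a normal scale is θ = Φ(0.3/√2) = 0.584, or 0.084 above 0.5. The signals lost above (0.005-0.008, 0.016-0.018 and 0.024-0.025) are about 6-10%, 19-22% and 29-30% of that.

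**The case against.** Four counter-arguments deserve weight.

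- **Matching.** Donors are the patients closest on the sick patient's own history. A reader might infer that untestable survivors are scored as near-average. The documents do not support that in general: when only week 48 is missing the imputed change is still about twice the cohort mean of -5. Near-average fits only loss from the first post-baseline visit. This objection stands and limits the size, but it does not remove the error.
- **The walk test.** A reader might infer that a patient unable to walk is given a typical distance for the endpoint "Change from baseline to week 48 in distance walked in the 6MWT". The missing-value section does not name that endpoint, and the Secondary endpoints section offers rank ANCOVA only as an example. Nor is it stated whether inability is recorded as missing or as 0 m; if it is 0 m, the rule never applies. The firm point is therefore FVC. Power figures for the walk test would also borrow an effect size and alpha set for FVC, so none are given.
- **Other endpoints capture worsening.** Time to disease worsening counts respiratory hospitalisation, transplant and clinical deterioration, which can be met through new oxygen therapy. True, but it is secondary and does not correct the primary score.
- **The analysis plan may deal with it.** It may add analyses. The primary rule, however, is fixed here in detail; it is a stated choice and not an omission.

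**Conclusion.** The point holds for the primary FVC analysis: the rule disregards why a living patient's value is missing, and it systematically scores survivors too ill to be tested too well. Against a true position near the 4th percentile, the score is about the 14th-19th, 33rd-38th or 50th percentile, depending on when testing stops. These figures rest on assumed visit times, variances and an 8% untestable fraction, with untestable patients taken to be the worst by true change. A weaker link between inability and decline would narrow the gap.

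A reader might infer that the rule favours pirfenidone. The documents do not fix a direction. Benefit is diluted if inability is commoner on placebo, harm is masked if it is commoner on pirfenidone, and under no treatment effect equal rates give no shift. The arm fractions in Step 3 are illustrations only.

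**What to change.** 1. Record in the e-CRF, if it does not already do so, why each FVC value is missing, separating inability due to lung disease from other reasons.
2. Keep the present rule as the primary analysis.
3. Pre-specify one sensitivity analysis of the primary endpoint that ranks living patients untestable for lung-disease reasons just above the deaths, ordered by time of failure. Values missing for other reasons stay under the present rule.
4. State whether the rule also governs secondary endpoints analysed by rank ANCOVA. If it does, run the same sensitivity analysis for DLCO and the walk-test endpoints, and state that inability to walk because of lung disease is an observed 0 m and not a missing value.

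The cost is one e-CRF field and one extra analysis. Sample size and the primary test do not change. With 74 patients randomised by May 2017 out of 374 planned, reasons could still be collected prospectively for most. The downside is that if inability is equally common in both arms, the sensitivity analysis has lower power than the primary, and it should be read with that in mind.

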### Secondary endpoints

Secondary outcomes will be analyzed by using appropriate statistical methods, e.g. Kaplan-Meier estimates and rank ANCOVA. Additional analyses will be described in detail in a statistical analysis plan (SAP) before data base closure.

